## Abstract

**Background:**

The prevalence of obesity in childhood is increasing worldwide and may be affected by genetic factors and the lifestyle (exercise, nutrition behavior) of expectant parents. Lifestyle factors affect adipokines, namely leptin, resistin, and adiponectin as well as cytokines such as tumor necrosis factor alpha (TNF-α) and interleukin-6 (IL-6), which are involved in the regulation of maternal metabolic homeostasis, glucose metabolism, and the development of insulin resistance, metabolic syndrome, gestational diabetes mellitus, and hypertension. However, studies focusing on the effect of exercise or a combination of parental exercise and nutrition on the above-mentioned markers in newborns (venous cord blood) and especially on the long-term development of infants’ weight gain are lacking. The study will investigate the effects of a multimodal intervention (regular exercise, diet) on parental and childhood adipocytokines (leptin, resistin, adiponectin, TNF-α, IL-6, BDNF). The effect of a lifestyle-related change in “fetal environmental conditions” on the long-term weight development of the child up to the age of two will also be assessed.

**Methods/design:**

A randomized multi-center controlled trial will be conducted in Germany, comparing supervised aerobic and resistance training 2x/week (13th to 36th weeks of gestation) and nutritional counseling (6th to 36th weeks of gestation) during pregnancy with usual care. Thirty women (pre-pregnancy Body Mass Index ≥25 kg/m^2^, 6th–10th week of gestation) will be included in each group. Maternal anthropometric and physical measurements as well as blood sampling will occur at the 6th–10th, 13th–14th, 21st-24th, and 36th week of gestation, at delivery as well as 8 weeks and 24 months postpartum. Neonatal measurements and umbilical blood sampling will be performed at birth. Maternal and infants’ weight development will be assessed every 6 months till 24 months postpartum. A difference in childhood BMI of 1 kg/m^2^ at the age of two years between both groups will be assumed. A power size of 80% using a significance level of 0.05 and an effect size of 1.0 is presumed.

**Discussion:**

A better understanding of how lifestyle-related changes in the fetal environment might influence infants’ outcome after two years of life could have a profound impact on the prevention and development of infants’ obesity.

**Trial registration:**

The trial is registered at the German Clinical Trial Register (DRKS00007702); Registered on 10th of August 2016; retrospectively registered https://www.drks.de/drks_web/navigate.do?navigationId=trial.HTML&TRIAL_ID=DRKS00007702

## Background

The prevalence of overweight (Body Mass Index ≥25 kg/m^2^) and obesity (Body Mass Index ≥30 kg/m^2^) is increasing worldwide in every age group [1]. In Germany, the number of obese women of child-bearing age has increased especially over the last 25 years from 8.1% in 1990/1991 (25–34-year-old women) to 17.3% (30–44-year-old women) in 2014/2015 [2–4]. When obese women become pregnant they are at increased risk of several perinatal and postpartum complications such as excessive weight gain, gestational diabetes, preeclampsia, pregnancy-induced hypertension or fetal macrosomia [5, 6]. In addition, maternal overweight, excessive weight gain, and gestational diabetes during pregnancy are associated with obesity in childhood and adolescence in the child [7, 8]. Furthermore, children of overweight mothers are at increased risk for long-term metabolic dysfunctions such as hypertension, insulin resistance or metabolic syndrome [8, 9].

Epidemiological, clinical (animal), and experimental studies suggest that maternal lifestyle during pregnancy influences the metabolic, pro-inflammatory, and neurotropic pattern of the unborn child [10–12]. For instance, lifestyle factors have shown to affect adipokines, namely leptin, resistin and adiponectin as well as cytokines such as tumor necrosis factor alpha (TNF-α) and interleukin 6 (IL-6) [13, 14]. These, in turn, are involved in the regulation of maternal metabolic homeostasis and glucose metabolism, and the development of insulin resistance, metabolic syndrome, gestational diabetes mellitus, and hypertension [13].

Reports show that dietary patterns are associated with adiponectin, leptin, and insulin resistance [14–16]. For example, high intakes of fat are negatively associated with adiponectin levels and positively associated with leptin concentrations during pregnancy [16].

However, there are few reports about the interplay of lifestyle factors, in particular maternal exercise, during pregnancy and their effects on biomarkers in mother and offspring [17, 18].

Moreover, Reilly et al. [19] and Pato et al. [20] documented that paternal overweight is another risk factor for the development of juvenile obesity. In a cohort study among 4871 mothers, fathers, and their children, Gaillard et al. [21] evaluated the associations of paternal as well as maternal pre-pregnancy body mass index (BMI) with childhood body fat distribution and cardiometabolic outcomes. It was found that a higher maternal and paternal pre-pregnancy BMI was associated with an adverse cardiometabolic profile in offspring, although stronger associations were present for maternal pre-pregnancy BMI. These findings were confirmed by Santos Ferreira et al. [22]. In the last decade, research increasingly focused on epigenetic effects of lifestyle factors on offspring. In a systematic review, Dunford and Sangster [23] documented that newborns from obese fathers displayed altered methylation overall and significant hypomethylation at the Insulin-like Growth Factor 2 gene. Furthermore, altered offspring DNA methylation levels were associated with high maternal pre-pregnancy BMI [23]. Altered methylation outcomes at multiple imprint regulatory regions in children born to obese parents, compared with children born to non-obese parents, were also found by Soubry et al. [24]. They conclude that parental lifestyle factors and overnutrition have a preconceptional influence on the (re)programming of imprint marks during gametogenesis and early development [24].

Beside these findings, there is a lack of studies focusing on the effect of exercise or a combination of parental exercise and nutrition on the above-mentioned markers in newborns (venous cord blood) and especially on the long-term development of infants’ weight gain. Most previous studies have investigated maternal lifestyle changes but did not take paternal influences into account [25, 26]. Additionally, most of these interventions only used counseling sessions and information brochures [27, 28], and because of substantial methodological variations (e.g. content, duration, frequency, outcome parameters) results are inconsistent [29]. Paternal or transgenerational effects have predominantly been investigated in animal models with a main focus on nutrition [30–32]. In humans, only birth cohort studies have examined paternal lifestyle factors in combination with selected blood samples [33].

Based on the sparse data available, we designed a multi-center, two-arm, randomized controlled trial to evaluate the effect of a multi-component, family-based program during pregnancy on maternal, paternal, and neonatal biomarkers as well as how lifestyle-related changes in the fetal environment might influence infants’ outcome after two years of life. More specifically, the importance of a healthy lifestyle, in particular regular exercise and diet, will be investigated. The aim of this study is to examine the influence of a lifestyle intervention in overweight/obese mothers and fathers on parental metabolic functions and infants’ weight two years after birth. The purpose of this paper is to present the design and methodology of the ADEBAR (Adiposity prevention through an exercise- and nutrition-based family program) study.

## Methods/design

### Study design and setting

The ADEBAR study is a multi-centre, two-arm, randomized controlled trial (intervention versus control group) with the primary purpose of prevention. The program will take place at three hospitals in the Rhine region (Cologne, Düsseldorf, and Bonn) in Germany. The intervention period will last approximately 30–32 weeks (8 months) depending on the date of delivery. Mothers, fathers, and their offspring are being followed until the infant is two years of age. A schematic timeline and SPIRIT timetable of the study is presented in Fig. 1 and Fig. 2.

**Fig. 1 Fig1:**
[figure not shown]
Schematic Timeline of the ADEBAR study

**Fig. 2 Fig2:**
[figure not shown]
Schedule of enrolment, interventions, and assessments

We will perform a block randomization with a block size of six including an equal number of participants for all groups within each block (3:3). This ratio was chosen as it is expected to reduce bias and allocate participants evenly between the intervention and the control group [34].

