#### Sample size

Power analysis was done based on recommendations of weight gain in German children at 24 months after birth [37]. Normal weight gain (50th percentile) after subtraction of birth weight is nine kilograms at the age of 24 months. The BMI shows a difference of 1 kg/m^2^ at this time point (50th percentile). Therefore, a difference of 1 kg/m^2^ at the age of two years between the intervention and the control group will be assumed. To detect this difference in proportions with 80% power (GPower analysis) using a significance level of 0.05 and an effect size of 1.0, 48 women are needed. Calculating with a drop-out rate of 25% during the program, 60 women are required and planned to be recruited for this study.

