#### Recruitment

Participants will be recruited by hospital- and community-based obstetricians in Cologne, Düsseldorf, and Bonn. To inform eligible women about the study, an information brochure with inclusion criteria and overall information will be used by hospital staff and obstetricians. If a woman shows interest, the recruiting centre will inform the project coordinator to contact her and provide further information about the randomization (intervention or control group). The date of the first enrolment was the 21st of June 2016. The recruitment is ongoing.

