### Intervention

Depending on the place of recruitment, the nutrition counseling and exercise program will take place either in Cologne, Bonn or Düsseldorf in a conference room or at a gym, respectively. The intended group size will be 30 participants.

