#### Statistics

The main variable (BMI at 24 months) will be analyzed by covariance analyses evaluated by the factor group, breastfeeding, and smoking as well as covariances of parental age, paternal BMI, socioeconomic status, breastfeeding, and potential pregnancy-induced diseases (e.g. gestational diabetes mellitus, pregnancy-induced hypertension (PIH)). The significance level alpha will be set at < 0.05 for all analyses. All confidence intervals will be estimated at 95%. Missing data will be calculated according to the LVCF approach (Last Value Carried Forward). Analyses will be carried out as per-protocol-analyzes and intention-to-treat analyses (ITT). Spearman and Pearson correlation procedure will be used to assess relationships between maternal data (physical activity in METs, eating habits, weight gain, blood samples) and neonatal data (birth weight, length, head circumference, Apgar scores, cord blood sample) as well as infants’ development. Multiple linear regressions will be performed for neonatal measures to determine correlations with maternal and paternal lifestyle factors. The model will include group (intervention yes/no) as well as maternal and paternal characteristics as possible confounders. Explained variance (r-squared) for the linear regression model will be reported as model fit statistic.

Statistical analysis will be performed using SPSS 24.0 data-analysis software (Statistical Product and Service Solutions 24.0) and data analysis will be blinded.

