## Discussion

Overweight and obesity in pregnancy is associated with adverse short- and long-term health effects for both mother and infant. Due to an increasing number of overweight and obese German women of child-bearing age, it is crucial to develop new strategies to prevent obesity in pregnancy and therewith in childhood. Recent studies indicate that, in addition to the mother, the father also plays a pivotal role in the development of childhood obesity. Therefore, we included the father in our intervention program and suggest that future studies should take paternal factors into account.

However, besides the innovations and strengths of our study design there is also a limitation. We are aware that blinding is an important aspect of all studies, which contributes to avoiding and preventing conscious and unconscious bias (for example performance bias or detection bias) in the design and conduction of a trial. Due to our design and recruitment all participants will know which treatment (intervention or control) they will receive. Due to the fact that all participants will be recorded via a predetermined code, at least data input as well as data analysis will be blinded.

To conclude, the main aim of our study is to determine whether regular physical activity and nutritional counseling during pregnancy has an impact on infants’ BMI and infants’ development two years after birth. Our findings will help to detect new influential lifestyle factors during pregnancy which may prevent obesity in early life. Furthermore, the results will provide a basis for new recommendations for action. Therefore, no later than five years after the last recruitment, we will try to deliver the first results and recommendations for sharing purposes.

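### A single block size of six, published while recruitment continues, lets anyone who follows the allocations know about a quarter of them in advance

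*Protocol article*

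**What the plan says.** Four statements in the article bear on this point.

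- **Scheme.** The text after Fig. 2 (Study design and setting) specifies "block randomization with a block size of six including an equal number of participants for all groups within each block (3:3". It gives one size and no variation, and justifies the choice as a way to limit bias and keep the arms even.
- **Recruitment route.** The Recruitment section describes the next step for an interested candidate as follows: "the recruiting centre will inform the project coordinator to contact her and provide further information about the randomization (intervention or control group". That section also gives a first enrolment in June 2016 and says that recruitment is ongoing.
- **Blinding.** The Discussion says that "all participants will know which treatment (intervention or control) they will receive" and claims blinding only for data input and data analysis.
- **Size.** Under Sample size, "60 women are required and planned to be recruited for this study". The Intervention and Control group sections each intend 30 participants.

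The article does not say who holds the allocation list, when an allocation is released, or whether lists are separate by centre.

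**The concern.** A 3:3 block balances the arms. It also means that once one arm has filled its three places, every remaining place in the block belongs to the other arm. When the size never changes and is in print, a person who has followed the allocations can tell when that has happened. Arms are known after allocation, so the preceding sequence can in principle be reconstructed.

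The stake is selection bias. Someone who talks to women before they join, and who knows or suspects the next arm, can encourage or delay particular women, even without meaning to. In a trial of 60, modest steering on maternal weight or motivation could carry into infant BMI at two years. The planned adjustment would not reliably remove it. The primary analysis is described as "covariance analyses evaluated by the factor group, breastfeeding, and smoking", with further covariates that include paternal BMI, but the list names neither maternal pre-pregnancy BMI nor motivation.

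**Working it through.** **Inputs**

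- Block of 6 with 3 places per arm: text after Fig. 2.
- 60 women in total, 30 per arm: Sample size, Intervention, Control group.
- Planning difference of 1 kg/m² in infant BMI at two years: Sample size.
- Difference *d* in mean infant BMI between women steered to one arm and women steered to the other: **assumption**, 0.5 kg/m², range 0.25 to 1.0. The article gives no figure for this.

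**Step 1. The plan's own figure.** 60 / 6 = 10 complete blocks, and 10 × 3 = 30 per arm. This agrees with the stated group sizes. The article states no predictability figure.

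**Step 2. Predictability of a fixed block of six.** There are C(6,3) = 20 equally likely sequences. The observer is assumed to know the block size, the block starts and all preceding allocations. A place is certain once one arm has used its three places. The best guess is the arm with more places left, or a coin toss if they are equal.

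| Place in block | Probability certain | Probability best guess is right |
|---|---|---|
| 1 | 0 | 0.5 |
| 2 | 0 | 3/5 = 0.6 |
| 3 | 0 | 0.4 × 3/4 + 0.6 × 1/2 = 0.6 |
| 4 | 2/20 = 0.1 | 0.1 × 1 + 0.9 × 2/3 = 0.7 |
| 5 | 8/20 = 0.4 | 0.4 × 1 + 0.6 × 1/2 = 0.7 |
| 6 | 1.0 | 1.0 |
| Sum | 1.5 | 4.1 |

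Certain: 1.5 / 6 = 25%, or 10 × 1.5 = 15 of 60 women. Guessed correctly: 4.1 / 6 = 68.3%, against 50% under simple randomisation. These are averages: 60% of blocks have one certain place, 30% have two and 10% have three.

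**Step 3. If lists are separate by centre (not stated).** Incomplete last blocks lower the share slightly:

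- 20/20/20 women: 3 × (3 × 1.5) = 13.5 of 60 = 22.5%.
- 40/10/10 women: (6 × 1.5 + 0.1) + 2 × (1.5 + 0.1) = 12.3 of 60 = 20.5%.
- 18/18/24 women: only complete blocks, 15 of 60 = 25%.

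**Step 4. Possible bias in the arm difference**

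- Only certain places steered: bias = 0.25 × *d*. For *d* = 0.5 this is 0.125 kg/m²; for 0.25 and 1.0 it is 0.06 and 0.25. Against 1 kg/m² that is 6 to 25%.
- Every guess acted on: bias = (2 × 0.683 − 1) × *d* = 0.367 × *d*. For *d* = 0.5 this is 0.18 kg/m²; for 0.25 and 1.0 it is 0.09 and 0.37. Places where the guess is a coin toss contribute nothing, since 2 × 0.5 − 1 = 0. This is an upper bound.

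**Step 5. Randomly varying block sizes.** Simulation of 4,000 trials of 60 women, with an observer who knows the set of sizes and the full history but not the order of sizes:

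| Block sizes | Certain | Best guess right | Bias at *d* = 0.5, certain places only | Bias at *d* = 0.5, every guess |
|---|---|---|---|---|
| 6 fixed | 25% | 68.3% | 0.125 | 0.18 |
| 4 and 6 | 5.7% | 69.0% | 0.057 × 0.5 = 0.03 | 0.380 × 0.5 = 0.19 |
| 4, 6 and 8 | 2.3% | 67.7% | 0.023 × 0.5 = 0.01 | 0.354 × 0.5 = 0.18 |

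Varying the sizes removes most of the certainty and leaves guessing almost unchanged.

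**The case against.** The strongest reply is that the key link is not in the article. The Recruitment section says only that the coordinator contacts the woman and tells her about the randomisation. It does not say that the coordinator sees allocations, holds the list or decides on enrolment; someone else may hold it. **This stands**, and it makes the point conditional.

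A second reply is that lack of participant blinding is not lack of concealment. The Discussion says that women will know their treatment, not that upcoming assignments are disclosed. **This also stands.** The article's silence on concealment is no fault, since the full protocol may describe it.

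A third is that the bias figures rest on an assumed *d*, and that a recruiter would seldom find a suitable woman for every place. The narrow gestational window for entry also limits delay. **This stands as a limit on size**: 0.18 kg/m² is an upper bound, not an estimate.

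A fourth is that, by the same arithmetic, mixed blocks barely reduce the every-guess bias, so most of the protection comes from concealment. **This is partly right.** Certainty still falls from 25% to about 6% or 2%, and knowing the next arm is a different temptation from guessing it. It does mean that varying sizes should go together with late release of the allocation.

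None of these replies touches the core. The single block size is a stated choice, it is in print, and recruitment is continuing.

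**Conclusion.** The point holds in conditional form. With a fixed, published block of six, a person who knows the block starts and the preceding allocations knows 25% of allocations in advance on average (about 20 to 25% with separate centre lists) and can guess 68%. If only certain places were steered, the bias would be about 0.125 kg/m² (0.06 to 0.25); the upper bound is about 0.18 (0.09 to 0.37), against a planned difference of 1 kg/m². Both rest on the assumed *d* of 0.5 (0.25 to 1.0).

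A reader might infer three stronger things that the article does not support:

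- That the coordinator does foresee allocations, or that concealment is absent. The article shows only that one role is well placed to follow them.
- That a bias of this size is expected. The figures show what steering could do, not that it occurs.
- That randomisation is not stratified by centre. The article is silent, and silence in a condensed account is not evidence.

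This is a modest weakness that is cheap to correct and worth correcting while women are still being enrolled.

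**What to change.** For all participants still to be randomised, replace the fixed blocks with randomly varying sizes (for example 4 and 6, or 4, 6 and 8). Do not disclose the sizes or the list to anyone who recruits or enrols. Because the size of six is already public, keeping it quiet from now on would not help; the scheme itself has to change. If the full protocol does not already require it, release each allocation only after consent and the baseline assessment are recorded.

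The cost is a new computer-generated list and a short protocol amendment. An incomplete block can leave a small imbalance, at most half its size: 4 women for a block of 8, against 3 for the present block of 6. Separate lists by centre could each leave one incomplete block. The article does not say how many women remain to be randomised, so the benefit for the whole trial cannot be sized; it shrinks as recruitment nears completion.

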### Participants

#### Inclusion and exclusion criteria

Women with a pre-pregnancy BMI [35] of ≥25 kg/m^2^, a singleton pregnancy, and a gestational age between 6 and 8 weeks, who were previously sedentary, are without pre-existing conditions such as heart disease, and who are currently not consuming alcohol or using medication for mental health disorders, will be recruited. At 13 weeks of pregnancy, women will receive a physician’s clearance to participate in physical activity. For further participation, they should have no contraindications to exercise during pregnancy according to the American College of Obstetrics and Gynecology [36]. Women with pre-existing diabetes, hypertension, or comorbidities known to affect fetal growth will be excluded from the study as well as women who are not proficient in German. Monthly obstetric check-ups will ensure maternal and fetal well-being.

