#### Nutrition counseling

Every nutrition counseling will be an extra appointment and is not part of the usual prenatal care appointments.

Pregnant women and their partners will be invited to a lecture about healthy diet during pregnancy at 8 weeks of gestation. This lecture will be followed-up by a 24 h dietary recall [38] to analyze individual energy intakes. This data will be entered and processed using the Prodi-Software® 6.2 (Science publishing society Stuttgart 2013, Germany) to calculate daily amounts of foods and nutrients. Based on this data, individual dietary counseling for the mother and, if possible, for the father will take place at 10 to 12 weeks of gestation. Individual counseling will be repeated at 16 and 24 weeks of gestation based on further 24 h dietary recalls. Additionally, group dietary counseling will consist of five sessions (weeks 14, 20, 30 and 36 of gestation, 8 weeks postpartum) and will be based on recommendations from the Network “Healthy Start – Young Family Network” [39]. Each session will last 60 min and will be led by a specially trained dietician.

After successful participation in the intervention, the families will receive a shopping voucher.

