#### Exercise protocol

The exercise program is not part of the usual prenatal care appointments. From the 13th to at least the 36th week of gestation, women will carry out a supervised exercise program (aerobic exercise and strength training) twice a week for 90 min. Resting blood pressure will be measured in the first 10 min of each session before starting the exercise protocol. Every exercise session will include a 10–15 min gradual warm-up and a 10–15 min cool-down including low intensity calisthenics, relaxation and stretching (avoiding muscle pain) of most muscle groups (upper and lower limbs, shoulder and trunk) as well as 10 min of pelvic floor exercises. The main part of the session will last at least 40 min. Depending on the women’s condition, the main part will be devided into two to three parts of 20 or 15 min, respectively, with a little break in between the parts to avoid physical overload. The duration of the parts may be gradually increased as the intervention progresses.

Aerobic exercise sessions will consist of Nordic walking and walking. Each woman will wear a portable heart rate monitor (POLAR Electro Oy, Kempele, Finnland) during each session to stay within the recommended heart rate zone reported by Davenport et al. [40]. Furthermore, the talk test will be used to ensure that exercise is performed at moderate intensity [36].

Strength training will consist of exercises targeting major muscles groups in the upper body, trunk, and lower body by using resistance bands and light dumbbells. In total, the participants will perform two to three sets with 12–15 repetitions of 8–10 muscular strength exercises [41]. The workload and exercises will be documented for each woman on an exercise sheet. The intensity of the exercises will be set according to each woman’s perceived effort using the Borg scale [42]. Participants will progressively increase the resistance of each exercise. In addition, women will be encouraged to take up leisure-time activities such as walking for an additional 30 min per week to reach the recommended level of 210 min of exercise per week [36, 43].

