### Control group

The intended group size will be 30 participants. Women allocated to the control group will neither be encouraged nor discouraged from exercising. They will undergo routine antenatal care and receive standard nutrition and activity guidelines from their obstetricians. To improve compliance, women from the control group will participate in a relaxation class, which includes breathing techniques and guided meditation once a week. The control group will undergo the same physical assessments as the intervention group.

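### Absence of contraindications to exercise is checked at week 13, after allocation, as a condition of continuing; the text secures neither equal application in both arms nor follow-up of women not cleared

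*Protocol article*

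**What the plan says.** The section on inclusion and exclusion criteria recruits women at "a gestational age between 6 and 8 weeks". It then adds a later step: "At 13 weeks of pregnancy, women will receive a physician’s clearance to participate in physical activity". The next sentence makes the result a condition: "For further participation, they should have no contraindications to exercise during pregnancy", judged by an obstetric college's guideline. Neither sentence names an arm.

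Under Nutrition counseling, part of the Intervention section, couples "will be invited to a lecture about healthy diet during pregnancy at 8 weeks of gestation", and individual counselling for the mother and, "if possible, for the father will take place at 10 to 12 weeks of gestation". The abstract gives the intervention periods as "13th to 36th weeks of gestation) and nutritional counseling (6th to 36th weeks of gestation", compared with usual care. The Exercise protocol section agrees on the start of exercise: "From the 13th to at least the 36th week of gestation, women will carry out a supervised exercise program".

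Of controls, the Control group section says: "Women allocated to the control group will neither be encouraged nor discouraged from exercising". They attend a weekly relaxation class and have the same physical assessments as the intervention arm. Whether those assessments include the week 13 clearance is not stated.

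The Statistics section plans both per-protocol and ITT analyses, with the last value carried forward for missing data.

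**The concern.** A condition for being in a randomised trial should be settled before allocation. Here one is settled afterwards, and failing it appears to end participation. Two things are at stake.

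First, randomised women whose participation ends at week 13 have no child yet. Unless follow-up continues, no infant BMI is collected, and neither the ITT label nor carrying values forward can supply one.

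Second, the clearance has an obvious practical use only where exercise is given. A centre has a plain reason to look for contraindications in women about to start training and less reason in women attending a relaxation class. Participants know their arm, and the Discussion describes only data input and analysis as blinded. If the search were keener in one arm, the women remaining would no longer be comparable. Should those removed carry higher obstetric risk, which is plausible but not documented, the comparison would tilt toward the intervention.

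**Working it through.** The point rests on the order of events, so there is no figure in the plan to reproduce.

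**Order of events (week of gestation)**

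| Week | Event | Source |
|---|---|---|
| 6–8 (abstract: 6–10) | Recruitment | Inclusion and exclusion criteria; abstract |
| 8 (abstract: from 6) | First nutrition contact, intervention arm | Nutrition counseling; abstract |
| 10–12 | Individual dietary counselling | Nutrition counseling |
| 13 | Clearance; condition for continuing | Inclusion and exclusion criteria |
| 13 | Exercise starts | Exercise protocol |

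The text does not date randomisation. But counselling given to one arm and compared with usual care cannot begin before allocation is known, so allocation falls no later than about week 8. The check follows 13 − 8 = 5 weeks after the first intervention contact, or 13 − 6 = 7 weeks after the abstract's earliest start.

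**If the check were applied in one arm only (illustration)**

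The documents give no rate of failed clearance and no BMI for the children concerned, so both are assumed. Let q be the share of the intervention arm removed, and D the excess in BMI, in SD units, of their children over the rest. With no treatment effect, the full control arm has mean m + qD and the reduced intervention arm has mean m, so

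bias = q × D.

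With 24 women per arm (the plan's 48 ÷ 2) before removal, SE = √(1/[24(1 − q)] + 1/24) in SD units. Two-sided type I error is P(Z > 1.96 − bias/SE) + P(Z < −1.96 − bias/SE).

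| q | D | Removed of 30 | Bias (SD) | Type I error |
|---|---|---|---|---|
| 5% | 0.5 | 1.5 | 0.025 | 0.051 |
| 10% | 0.5 | 3 | 0.05 | 0.053 |
| 10% | 1.0 | 3 | 0.10 | 0.063 |
| 20% | 1.0 | 6 | 0.20 | 0.100 |

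Worked row (10%, 1.0): SE = √(1/21.6 + 1/24) = 0.297; bias/SE = 0.10/0.297 = 0.337; type I error = P(Z > 1.623) + P(Z < −2.297) = 0.052 + 0.011 = 0.063.

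The Sample size section pairs a difference of 1 kg/m² with an effect size of 1.0, which implies an SD of 1 kg/m². On that SD the biases read directly as kg/m².

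**If the check is applied equally in both arms**

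The differential bias is absent. What remains is loss of outcome data: 60 × 5% = 3 women, or 60 × 10% = 6. The plan recruits 60 to end with 48, an allowance of 12 for all causes. The text does not say whether women not cleared are counted in it.

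**The case against.** A reader might infer that only the exercise arm is screened. The documents do not support that. The clearance stands in the section common to all participants and refers to women without an arm, and controls are promised the same physical assessments. That the Control group section does not repeat the clearance proves little, since it repeats no other common criterion. Unequal screening is a risk the text leaves open, not something it prescribes. This part of the objection stands, and the point is limited accordingly.

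The condition for continuing follows directly on a sentence about clearance for physical activity, so it could mean continuing in the exercise sessions only. That reading is possible. Placement under the eligibility criteria favours the wider one, and if the narrower is meant, one sentence would settle it.

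Entry criteria already exclude pre-existing diabetes, hypertension, heart disease and conditions affecting fetal growth. Much high-risk disease is therefore screened out beforehand, and how much of the guideline's list can be assessed at entry cannot be judged from the article. This stands: it lowers the likely number affected and means the early check can only cover what is assessable then.

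The timeline and schedule figures are not shown and may date allocation. They could not place it after counselling given to one arm without contradicting the text.

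Finally, the Drop-out criteria section states other post-allocation exclusions more plainly, and an ITT analysis is planned. Both are true. But this condition lies outside that list, and an ITT analysis needs outcomes that someone has collected.

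**Conclusion.** The point holds in a limited form. On the natural reading, an eligibility condition acts about five weeks after intervention-only treatment begins and so works as a post-randomisation exclusion. The text does not ensure that it is applied alike in both arms, or that women who fail it are followed.

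The size cannot be estimated from the documents. The range of 0.025 to 0.20 SD depends wholly on assumed removal rates and risk differences, and on removal from one arm only. A reader might go further, assume 10% removed with children 2 kg/m² heavier, and conclude that a fifth of the 1 kg/m² target is bias (0.10 × 2 = 0.2). That excess would be two SDs on the plan's own scale, in women already screened at entry, and nothing in the documents supports it. Nor do they establish that any bias favours the intervention. Under equal application there is no differential bias from this source, only lost 24-month outcomes.

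**What to change.** In the section on inclusion and exclusion criteria:

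1. Complete whatever part of this eligibility check is possible at the entry visit, before randomisation, and identically for every woman.
2. State that any week 13 check is made by the same rule in both arms.
3. State that a woman not cleared remains in her allocated arm, is followed to 24 months and is kept in the ITT analysis.

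The clinical decision on who may exercise stays with the physician and is unchanged.

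The cost is a checklist at an existing visit, a few sentences, and follow-up of the few women concerned. Some women may be screened out before randomisation. Some allocated to exercise will contribute data without exercising, which slightly dilutes the effect. As an illustration, if 10% of the intervention arm gained nothing at all, a true difference of 1 kg/m² would appear as 1 × (1 − 0.10) = 0.9 kg/m².
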